### Total Number of Study Sites/Total Number of Subjects Projected:

Seven sites/~1000-1500 patient data per site projected.

Central coordinating site: All India Institute of Medical Sciences (AIIMS Bathinda)

- PI: [name], Assistant Professor, Pharmacology, AIIMS Bathinda
- Co-PI: [name], Associate Professor, Anaesthesia, AIIMS Bathinda; [name] [name], Additional Professor, General Surgery, AIIMS Bathinda

Other participating sites:

- Postgraduate Institute of Medical Education and Research, Chandigarh (PGIMER Chandigarh)

Site PI: [name] [name], Associate Professor, Pharmacology, PGIMER Chandigarh

Site Co-PI: [name] [name], Assistant Professor, General Surgery, PGIMER Chandigarh

- Postgraduate Institute of Medical Sciences (PGIMS Rohtak)

Site PI: [name], Associate Professor, Pharmacology, PGIMS Rohtak

Site Co-PI: [name], Professor, General Surgery, PGIMS Rohtak

- Dayanand Medical College, Ludhiana

Site PI: [name], Professor, Pharmacology, DMC Ludhiana

Site Co-PI: [name], Professor and Head of Department, General Surgery, DMC Ludhiana

- Government Medical College & Hospital, Sector-32, Chandigarh (GMCH-32)

Site PI: [name], Professor, General Surgery, GMCH-32, Chandigarh

Site Co-PI: [name], Associate Professor, General Surgery, GMCH-32, Chandigarh

- Jawaharlal Nehru Medical College (JNMC), AMU, Uttar Pradesh

Site PI: [name] [name], Assistant Professor, Pharmacology, JNMC, AMU

Site Co-PI: [name] [name], Assistant Professor, Department of Surgery, JNMC, AMU

[name] [name], Department of Orthopedics, JNMC, AMU

- [name] Medical College, Hamirpur, Himachal Pradesh (H.P)

Site PI: [name], Associate Professor, General Surgery, [name] Medical College, Hamirpur

Site Co-PI: [name], Assistant Professor, Orthopedics, [name] Medical College, Hamirpur

- [name], Professor, Indian Institute of Management, Calcutta
- [name], Professor, Department of Community Medicine, Government Medical College, Manjeri, Malappuram, Kerala.

## Study Population

### Inclusion Criteria

1. Surgical patients undergoing elective or emergency procedure (open or laparoscopic) under general surgery, neurosurgery, orthopedics, pediatric surgery, plastic surgery, urology.

### Exclusion Criteria

1. Pregnant or lactating females
2. Immunocompromised patients including uncontrolled diabetic patients, cancer patients, on immunosuppressive therapy.
3. HIV/HBV/HCV infection
4. Patients with prolonged hospital stay >1 week and received multiple antimicrobials before the planned procedure.
5. Patients with dirty wounds
6. Pre-existing active infection at surgical site
7. Minor procedure performed under local anesthesia
8. Therapeutic hypothermia needed during intra-operative or post-operative period
9. Patients with American Society of Anesthesiologist (ASA) score of 6 (declared brain dead whose organs are being removed for donor purposes) (For ASA score refer to Annexure-V)

## Subject Completion/Withdrawal

The patients who take leave from hospital against medical advice (LAMA) will be contacted for follow-up at 30-days for the outcome.

If follow-up is not possible at 30 days after surgery, patients will be followed up as soon after this as possible.

### Early Termination Study Visit

The site(s) which is/are not complying with the study procedure and the surgeons not following the multimodal interventions as required, will be terminated from the study. No further data collection will be done for that site.

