## Secondary Objectives (or AIM)

1. To identify the system and health care professional behavioral factors contributing to surgical site infections
2. To co-develop multipronged interventions which can be applied in hospital settings in LMICs
3. To evaluate the impact of multipronged interventions on in-patient mortality and length of hospital stay
4. To evaluate the number of deaths prevented by adoption of multipronged interventions
5. To evaluate the number of ICU admissions averted and number of hospital readmissions averted within 30 days after discharge by adoption of multipronged interventions
6. To evaluate the effect of multipronged interventions on the antimicrobial consumption indicators Days of therapy (DOT).

[Days of therapy is defined as an aggregate sum of days for which any amount of a specific antimicrobial agent was administered to individual patient^13^]

1. To evaluate the percentage of patients receiving the correct surgical antimicrobial prophylaxis.
2. To evaluate the acceptance of these multipronged interventions and challenges in their implementation by health care professionals using in-depth interviews and a qualitative feedback assessment form.

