# Investigational plan

## General Scheme of Study Design and Study Plan:

Quasi-experiment (pre-post design) will be adopted.

The plan is to adopt a four- phased strategy using mixed-method approach, each addressing specific research question (Figure-1).

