The baseline data collection will be done by the trained research associate/ICN nurse for the patients undergoing surgeries as per inclusion/exclusion criteria and the baseline SSI rate in the setting will be calculated from the baseline data collected. The baseline data collection will be done using the standard case record form (CRF) designed for the study which will include collection of data on (but not limited to) parameters like type of surgery, American Society of Anesthesiologists (ASA) physical status score (refer to Annexure-V), timing and antimicrobial agent for surgical prophylaxis, duration of surgery, need for redosing of antimicrobial prophylaxis, and other defined parameters. In addition, the observation of practices of the care delivery team and observation of interactions among care team and patients will be done at this stage. This qualitative assessment will allow the research team to observe points that practitioners may not have reflected on or recollect during interviews. The baseline data collection phase will last for 6 months. No intervention or practice change will be applied in this phase.

**Outcome of Phase-I:** Expected outcome of Phase-I will be to identify the knowledge gaps in the practice, barriers and challenges in adoption of the surgical prophylaxis prevention guidance. The baseline data collection will be done in this phase (pre-intervention data) on the baseline SSIs rates and practice followed in the setting. These findings will be helpful in co-development of the multipronged interventions during Phase-II.

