### Phase-III (Deployment of the multipronged interventions):

Phase-III will involve deployment of the multipronged interventions and process evaluation.

**Deployment of multipronged interventions:** Multipronged interventions developed in phase-II will be implemented in Phase-III using the following strategies: training of healthcare professionals, identification of Surgical site infection prevention (SSIP)/Stewardship champions, review of implementation by the project advisory committee.

**A. Structured training curriculum and training manual**: The structured training modules will be developed as per the multipronged interventions co-developed in Phase-II. The training modules will be contextualized to the practice change needs and the training sessions will be conducted using interactive sessions. The assessment will be applied pre and post-training among the health care professionals undergoing training to assess the practice and knowledge change adopted from the training modules. The assessment will also indicate the need for re-training.

**B. Training**: The project steering group (comprising of multidisciplinary team of PIs from the sites, antimicrobial stewardship experts) will impart comprehensive training of the relevant health care professionals including the operation theatre nursing staff involved in surgery and patient care, the residents, anesthesiologists’ and the surgeons using the structured training modules and curriculum using 4-5 interactive sessions, didactic lectures for adoption of the multimodal interventions spanned over a period of two months. The health care professions undergoing training will be assessed for practice and knowledge change using pre-developed assessment module. The score of >80% in the training assessment will be considered adequate. If score of <80%, then either re-training session will be conducted or not included in the study.

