**C. Identification of SSIP/Stewardship Champions**: The “SSIP champions” will be identified for each setting by the site PI/Co-PI (could be ICN nurse/resident/surgeon who have leadership qualities and actively working in the surgery department). These SSIP champions will ensure the adoption of the multimodal interventions in their setting and will also assess the need of interim training or re-training in their respective sites. If the compliance to the multipronged interventions is not there at a particular site as assessed by the checklist of each patient, then re-training will be schedule. If non-compliance is persistent, then it will be communicated to the project advisory group. The process evaluation will be done by project advisory group and IDI will be conducted to understand the hurdles and challenges in adoption of these interventions and explained below.

**Process evaluation**: The compliance to the multipronged interventions as assessed by the SSIP champions will be evaluated by the project advisory committee. The SSIP champions will also evaluate whether the structural and system changes are in-place at respective sites and behavioural changes are adopted by the health care professionals. If there is non-compliance and is persistent, then the stakeholders will re-assess the acceptance of the co-developed multipronged interventions. In-depth interviews with the health care professionals will follow to understand the hurdles and challenges in accepting these interventions and troubleshooting iteratively. The multipronged interventions will be either adapted as per the challenges evolving or co-developed as per the site need or if only retraining will suffice, then re-training will be planned. The monitoring of the compliance to the multipronged interventions at each site using the checklist will be done by SSIP champions and reported to the project advisory group quarterly.

The intervention will continue with the help of SSI Champions and after the study is over also. The intervention and result assessment quarterly will go hand in hand and the impact assessment will follow.

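### Stopping data collection when surgeons or sites do not follow the package removes units from the post-intervention phase, so the before-after contrast can shift through selection alone

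*Protocol*

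**What the plan says.** Section 3.5.1 (Early Termination Study Visit) has two limbs. One covers sites that fall short on study procedures; the other covers surgeons who do not adhere to the package. The consequence is the same for both: they "will be terminated from the study. No further data collection will be done for that site". The section gives no threshold. It does not say whether one surgeon's termination ends collection for that surgeon's patients or for the whole site.

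Section 3.1.3 (Phase-III, Training) adds a filter on staff: "If score of <80%, then either re-training session will be conducted or not included in the study". The process evaluation in the same section answers persistent failure differently: "If there is non-compliance and is persistent, then the stakeholders will re-assess the acceptance of the co-developed multipronged interventions". Interviews, adaptation of the package or re-training follow.

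The design is stated in section 3.1: "Quasi-experiment (pre-post design) will be adopted". Of the six-month baseline, section 3.1.1 says: "No intervention or practice change will be applied in this phase". Section 3.9 compares post-intervention rates at the study centres with the baseline data, by wound class, using chi-square, t or Mann-Whitney tests. It also plans a subgroup analysis by fidelity. Table-1 in section 3.1.2 defines a fidelity level for patients who received none of the intervention.

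**The concern.** A surgeon cannot fail to follow a package that does not yet exist, so the surgeon limb of section 3.5.1 can act only after deployment. Only later collection stops; nothing withdraws what was already recorded. Followed as written, the plan sets a baseline from every site and surgeon against a post-intervention phase that has lost the units where adoption failed.

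Three things are at stake.

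- **SSI.** With no concurrent control, a change in who contributes patients cannot be told apart from an effect of the package.
- **Process endpoints.** Section 3.8 includes the percentage of patients with prophylaxis beyond 24 hours. The template package in Appendix-I makes discontinuation within 24 hours a mandatory step, although the final package may differ. If that step is kept, removing surgeons who do not follow it improves this endpoint by construction, with no assumption about infection risk.
- **The question answered.** An implementation study asks what happens when a package is deployed. After removal, the data answer what happens where it was adopted. The low-fidelity groups needed for the planned subgroup analysis are depleted too.

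Read literally, the stop also covers patients at a terminated site who are still within their 30- or 90-day follow-up. By contrast, section 3.5 pursues even patients who leave against medical advice.

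**Working it through.** **Planned sample size (section 3.11).** The inputs are 90% power, 5% two-sided significance, 15% loss, and rates of 8% to 5%, 12% to 8% and 30% to 20%. The pooled-variance formula for two proportions is

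n = [1.96·√(2·p̄(1−p̄)) + 1.2816·√(p₁(1−p₁)+p₂(1−p₂))]² / (p₁−p₂)²

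For clean surgery, p̄ = 0.065 and n = (0.6833 + 0.4460)² / 0.0009, about 1418. The other strata give 1181 and 392. Multiplying by 1.15 gives 1631 / 1359 / 451 per phase, against the stated 1630 / 1350 / 450. The planned numbers are reproduced and are not at fault.

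**Evaluable patients.** 0.85 × 1630 = 1385.5; 0.85 × 1350 = 1147.5; 0.85 × 450 = 382.5 per phase.

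**Selection with no true effect.** The protocol gives seven sites. It does not give the number removed (k) or the ratio of their SSI risk to that of the remaining sites (r), so both are assumed, with equal site sizes and clustering ignored. All seven sites contribute to the baseline at rate p. The remaining sites then have

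p_rem = 7p / (7 − k + k·r), and the false fall is p − p_rem.

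Worked for clean surgery (p = 0.08):

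- r = 1: p_rem = 0.08, so the fall is 0.
- k = 1, r = 0.5: 0.56 / 6.5 = 0.0862, a false *rise* of 0.6 points.
- k = 1, r = 1.5: 0.56 / 7.5 = 0.0747, a fall of 0.5 points.
- k = 2, r = 2: 0.56 / 9 = 0.0622, a fall of 1.8 points.

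**Chance of a significant fall.** This is Φ[(fall − 1.96·SE₀)/SE₁], with SE₀ pooled and SE₁ unpooled. For clean surgery with k = 2, r = 2 and the post phase refilled to 1385.5 by the remaining sites: SE₀ = √(2 × 0.0711 × 0.9289 / 1385.5) = 0.00977 and SE₁ = 0.00976. That gives (0.01778 − 0.01914)/0.00976 = −0.139 and Φ = 0.445. If the post phase shrinks to 5/7, the result is 0.374.

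| Sites removed, risk ratio | False fall in points (clean / clean-contaminated / contaminated) | P(significant fall), range over strata and over shrunken or refilled post phase |
|---|---|---|
| any number, 1.0 | 0 / 0 / 0 | 2.5% |
| 1, 1.5 | 0.5 / 0.8 / 2.0 | 7-9% |
| 1, 2.0 | 1.0 / 1.5 / 3.8 | 16-21% |
| 2, 1.5 | 1.0 / 1.5 / 3.8 | 14-21% |
| 2, 2.0 | 1.8 / 2.7 / 6.7 | 37-55% |

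In the last row the false falls are 1.78/3 = 59%, 2.67/4 = 67% and 6.67/10 = 67% of the planned effects.

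**Alternatives.** With every unit kept in both phases, the false difference is 0 and the error rate returns to nominal. Leaving the same sites out of both phases also removes the compositional bias. Power then falls from about 89% to about 84% (one site) or 77% (two sites), and the estimate is confined to adopters.

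**The case against.** Much of the case against a stronger reading stands.

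- **A reader might infer that the whole rule acts after deployment only.** It does not. Study procedures such as form completion and follow-up also run at baseline, so the site limb can act in either phase. Only the limb on following the interventions is confined to the post-intervention phase.
- **A reader might infer that terminated units' baseline patients are stated to remain.** No sentence says so. It follows from a stop on further collection only, a comparison with the baseline data, and the absence of any matching rule. An SAP could restrict the baseline to surviving units. It could not recover outcomes that were never collected, and its result would then apply to adopters only.
- **A reader might infer that the post-intervention phase contains only compliers.** The protocol records fidelity for each patient and analyses by it, so ordinary non-adherence stays in. Loss occurs where termination is actually used.
- **A reader might infer that sections 3.1.3 and 3.5.1 flatly contradict each other.** Re-assessment, interviews and re-training can be read as steps before termination as a last resort. The order and threshold are unstated, so this needs clarifying rather than correcting.
- **A reader might infer that data for the acceptance objective ("To evaluate the acceptance of these multipronged interventions and challenges in their implementation by health care professionals") are destroyed.** Information already gathered remains, and persistent non-compliance itself prompts interviews. At most, later interviews at a terminated site are lost.
- **The training rule is weaker evidence.** Re-training is its first-named option, and nothing says that a low scorer's patients are dropped.

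The larger scenarios also have no support in the documents, and removing single surgeons would affect a smaller share of patients than removing whole sites. None of this answers the core point: the protocol itself orders outcome collection to stop because the intervention was not followed.

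**Conclusion.** The point holds as a risk of differential attrition built into a conduct rule. If section 3.5.1 is applied to non-adherence and the baseline is used as section 3.9 describes, the two phases compare different sets of surgeons or sites, and the estimate moves from deployment towards adoption.

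For SSI, the documents do not establish size or direction. Under the stated assumptions the result runs from no bias at equal risk, through a 7-9% chance of a false significant fall (one site, 1.5 times the risk), to 37-55% (two sites, twice the risk). It reverses if the removed units have lower risk. It is tempting to conclude that the bias must favour the package. That requires non-adopters to have higher underlying SSI risk, which is plausible but not documented. For process endpoints that coincide with a mandatory step, the direction is clear without that assumption.

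This should be settled before deployment, because outcomes not collected cannot be restored at analysis.

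**What to change.** 1. In section 3.5.1, separate failure of study procedures (data unreliable or not supplied) from non-adherence to the interventions.
2. For non-adherence, delete the stop on data collection. State that case record form data and 30/90-day outcomes are collected for all eligible patients in both phases, whatever the adherence or training score of the surgeon or site.
3. State that the primary analysis compares phases regardless of fidelity.
4. If a site must close because study procedures failed, complete follow-up of patients already enrolled where possible. Add a sensitivity analysis with that site left out of both phases.
5. Make any complier-only analysis secondary, with the baseline restricted to the same sites and surgeons.
6. State how the training-score rule and the process evaluation in section 3.1.3 fit with termination in section 3.5.1: in what order, at what threshold, and whether a terminated surgeon affects only their own patients or the whole site.

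The cost is mainly protocol wording, since section 6 already budgets data collection staff at all seven centres. The estimated effect may be smaller because non-adopters count, but that is the effect of deploying the package.

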## Description of study evaluations/measurements/assessments

## Primary Endpoint

The rate of surgical site infection till 30 days after surgery (90 days if implant) using CDC definition of SSI in pre-intervention versus post-intervention phase for clean, clean-contaminated and contaminated surgeries (Annexure-II, III).

## Secondary Endpoints

1. The number of ICU admissions averted and number of readmissions averted in clean, clean-contaminated and contaminated surgeries by adoption of multipronged interventions
2. The length of index hospital admission in pre-intervention and intervention phase for clean, clean-contaminated and contaminated surgeries.
3. The antimicrobial consumption indicators (Days of therapy) in the pre-intervention and intervention phase for clean, clean-contaminated and contaminated surgeries.
4. The percentage of patients receiving single dose of antimicrobial prophylaxis in the pre-intervention and intervention phase for clean, clean-contaminated and contaminated surgeries
5. The percentage of patients receiving prolonged antimicrobial prophylaxis (>24 hours duration) in the pre-intervention and intervention phase for clean, clean-contaminated and contaminated surgeries
6. The percentage of irrational combinations of drugs (double gram positive, double gram negative or double anaerobic coverage) for surgical antimicrobial prophylaxis in the pre-intervention and intervention phase for clean, clean-contaminated and contaminated surgeries
7. The number of deaths prevented in clean, clean-contaminated and contaminated surgeries by adoption of multipronged interventions
8. Acceptance of these multipronged interventions and challenges in their implementation by healthcare professionals.

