**Figure 2: Development and standardization process of multipronged interventions**

**Intervention Standardization:** The steps of intervention standardization will include defining the type of standardization for each component and defining the limits of the standardization for each component^19^. The type and limits of the standardization will be set after consensus with the stakeholders and the project advisory group.

1. Type of standardization for each component and step can be classified into “mandatory” or “optional” or “prohibited”. “Mandatory” step must be performed under all circumstances and if not performed will be considered as protocol deviation; opposite is true for “Prohibited”. “Optional” step may or may not be performed at discretion of the participating surgeon.
2. Limits of standardization for each component can be set as “exactly” or “with boundaries” or “without boundaries (flexible)” based on the flexibility allowed for adoption by the health care professional. If mentioned as “with boundaries”, the component or step can be followed as per the amount of flexibility mentioned for each component of intervention. (Table -2)

**Intervention Monitoring:** The levels of fidelity will be defined and noted as per the levels mentioned in Table-1 after discussion with all the stakeholders. The discrepancy among the stakeholders will be resolved after discussion among each other for reaching to the final consensus. Based on the multipronged interventions, a checklist and standard data collection form will be developed. The check list developed will be used for assessing the level of fidelity and compliance to the multipronged interventions for each patient as shown is Appendix-I.

**Table-1**: Levels and type of intervention fidelity to be described for each component of the multipronged intervention^19^

| **Level of fidelity** | **Type and description** |
| --- | --- |
| Protocol deviation from intended intervention | Did not receive any intervention or received alternative intervention not being evaluated in the study |
| Deviation from component(s) of the intended intervention | Did not receive the component of the intervention or component of intervention delivered partially or component of intervention delivered in a different way than what is mentioned in the study protocol. |

The set of selected multipronged intervention package co-developed and standardized by all the stakeholders will be implemented among health care professionals.

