# Appendix-I: Template example of the components of Multipronged interventions and CheckLIST to be checked for each patient

The intervention components can be chosen based on observed practices in the clinical setting, gap analysis, the global guidelines for prevention of surgical site infections by WHO^2^, second edition 2018 and Clinical practice guidelines for antimicrobial prophylaxis in surgery which were recommended with “Strong” recommendations and “Moderate to Good” quality of evidence and easy to implement in the setting.

**Table-2:** Template intervention package (not necessarily the same interventions mentioned below)

| **Components of multipronged Intervention** | **Steps of the Intervention** | **Type of standardization** | **Limits of standardization** |
| --- | --- | --- | --- |
| Interventions for surgical infection prevention: four system interventions | Delivery of intravenous antimicrobial prophylaxis within 1 hour before incision (2 hour for vancomycin and fluoroquinolones) | Mandatory | Boundaries (Flexibility in choosing antimicrobial by the surgeon based on the type of surgery, patient factors, clinical practice and guidance documents) |
|  | Redosing of antimicrobial if interval >2 half-lives or if blood loss >1500 ml | Optional | Boundaries (Flexibility based on the duration of the surgery and type of the antimicrobial agent chosen for surgical prophylaxis) |
|  | Use of antimicrobial prophylactic agent consistent with published guidelines (Global guidelines for prevention of surgical site infections by WHO^2^, second edition 2018 and Clinical practice guidelines for antimicrobial prophylaxis in surgery^10^) | Mandatory | Boundaries (Flexibility in choosing antimicrobial by the surgeon based on the type of surgery, patient factors, clinical practice and guidance documents) |
|  | Discontinuation of prophylactic antimicrobial agent within 24 hours of surgery (within 48 hours for cardiothoracic procedures in adult patients): Post operative day- 1(POD-1) review | Mandatory | Flexibility allowed till 24 hours postoperative |
| Interventions for surgical care improvement: five behavioral interventions | Proper hair removal: No removal (if not hampering surgery) or use of clippers/depilator method. | Optional | Boundaries (Flexibility in choosing no removal or clippers or depilators) |
|  | Use of razors for hair removal | Prohibited (Considered inappropriate if razors used for hair removal) | Exactly (Not flexible) |

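### Secondary endpoint 4 (single-dose prophylaxis) makes no exception for intra-operative redosing, so better uptake of the template package's redosing step would lower it

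*Protocol*

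**What the plan says.** Section 3.8 of the protocol lists, as secondary endpoint 4, "The percentage of patients receiving single dose of antimicrobial prophylaxis in the pre-intervention and intervention phase", by wound class. No exception or further definition is given. Endpoint 5 is "The percentage of patients receiving prolonged antimicrobial prophylaxis (>24 hours duration) in the pre-intervention and intervention phase".

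Appendix-I, Table-2 gives a template package. One step is "Redosing of antimicrobial if interval >2 half-lives or if blood loss >1500 ml", typed Optional. Section 3.1.2 explains that an optional "step may or may not be performed at discretion of the participating surgeon". A second step, typed Mandatory, is "Discontinuation of prophylactic antimicrobial agent within 24 hours of surgery (within 48 hours for cardiothoracic procedures in adult patients"), with the limit "Flexibility allowed till 24 hours postoperative". Table-3 turns both into checklist items answered yes or no for each patient. Item 2 notes whether redosing was required. Item 4 notes the end of surgery and the time of the last dose.

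The baseline case record form in section 3.1.1 captures "need for redosing of antimicrobial prophylaxis". Section 4.1 lists redosing and, separately, details of post-operative antimicrobials among the data collected at baseline and after the intervention. Section 3.9 compares secondary outcomes after the intervention with baseline in order to judge its impact.

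**The concern.** Endpoint 4 is a raw dose count. It cannot tell a second dose given during a long or bloody operation from a second dose given on the ward. The first is a step that the template package contains. The second is the practice that the background describes as a problem (sections 1.1 and the synopsis rationale, on multiple-dose prophylaxis beyond one day).

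The package acts on both kinds of dose. If it increases redosing when a trigger is met and also reduces post-operative continuation, the two effects push endpoint 4 in opposite directions. The pre-post comparison could then show no change, or a decline, in a setting where practice moved as the package intends on both counts.

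**Working it through.** The protocol states no figure for this endpoint, so there is nothing to reproduce. The check sets the two rules side by side and then sizes the mismatch under assumed inputs.

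**1. Classification of the same patient under the two rules**

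| Patient | Checklist item 2 | Endpoint 4 |
| --- | --- | --- |
| No trigger, no post-operative dose | redose not required | counted as single dose |
| Trigger met, redosed, no post-operative dose | followed | not counted |
| Trigger met, not redosed, no post-operative dose | not followed | counted as single dose |
| Any post-operative dose | either | not counted either way |

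Rows two and three show the conflict. Row four limits its size: a patient with post-operative doses is already outside the count, so redosing changes nothing for that patient.

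**2. Formula**

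Let r be the share of patients who meet a redosing trigger, c the share of those who are redosed, and s the share of triggered patients with no post-operative doses. Take s as the same in both phases and unrelated to whether the patient was redosed. Then

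change in endpoint 4 = −r × (c after − c before) × s.

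**3. Numbers (all assumed; none is in the protocol)**

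Take r = 10% to 25% and c rising from 20% to 80%, a change of 0.60.

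- Upper bound, s = 1 (no triggered patient has post-operative doses): 0.10 × 0.60 × 1 = 6 points; 0.25 × 0.60 × 1 = 15 points.
- s = 0.20 (most triggered patients are continued after surgery): 0.10 × 0.60 × 0.20 = 1.2 points; 0.25 × 0.60 × 0.20 = 3.0 points.

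**4. How much real improvement this can hide**

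Let s now apply to all patients and be allowed to change. Endpoint 4 is then s × (1 − r × c).

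- With r = 25%, the factor 1 − r × c goes from 1 − 0.25 × 0.20 = 0.95 to 1 − 0.25 × 0.80 = 0.80. From s = 20%, endpoint 4 starts at 0.20 × 0.95 = 19.0%. It is still 19.0% when s has risen to 0.19 / 0.80 = 23.75%.
- With r = 10%, the factor goes from 0.98 to 0.92, and the break-even value of s is 0.20 × 0.98 / 0.92 = 21.3%.

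So a true gain of 1.3 to 3.75 points in patients with no post-operative doses would appear as no change. A smaller gain would appear as a decline.

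**5. Against sampling error**

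Section 3.11 plans 1630 clean and 1350 clean-contaminated patients per phase. The standard error of a difference in percentages, ignoring site effects, is at most √(2 × 0.25 / 1630) = 1.8 points and √(2 × 0.25 / 1350) = 1.9 points. A 6-point artefact exceeds three of these. At s = 0.20 and r = 10%, endpoint 4 would be 19.6% before and 18.4% after. The standard error in clean surgery is then √((0.196 × 0.804 + 0.184 × 0.816) / 1630) = 1.4 points, which is larger than the 1.2-point artefact. Whether the artefact is visible therefore depends on s.

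**6. Endpoint 5**

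The limit is 24 hours in both section 3.8 and Table-2. They differ only if the endpoint's clock starts at the first dose. For example, a dose 1 hour before incision, 3 hours of surgery and a last dose 22 hours after the end give 1 + 3 + 22 = 26 hours, although the last dose lies within the post-operative limit. Timed from the end of surgery, the value is 22 hours and the two agree. Section 3.8 does not name the starting point.

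**The case against.** The strongest reply is that there is no adopted package yet. Table-2 is labelled a template, and the real package is to be agreed by the stakeholders in Phase II. This stands: the conflict is with the template and becomes real only if the redosing step is kept. Endpoint 4 is already fixed, however, and redosing is recorded in the main data collection as well as in the template.

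Second, redosing is Optional, so omitting it is not a protocol deviation, and the protocol never calls a single dose a success or further doses a failure. Both stand. The favourable direction is inferred from the objective on correct prophylaxis in section 2.2 and from the background. The scoring conflict does not depend on the label, because a redose removes the patient from the count whether the step is optional or mandatory.

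Third, other measures remain. Endpoint 5, days of therapy and irrational combinations still describe practice, and an intra-operative redose does not by itself take prophylaxis past 24 hours. This stands, so it would be too strong to say that the endpoints cannot show the direction of change.

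A reader might also infer that endpoint 5 follows a different rule from the package. The documents do not support that. The limit is the same, and both the WHO process measure in section 1.1 and checklist item 4 time it from surgery. The one different limit, 48 hours, concerns cardiothoracic procedures, which section 3.4.1 does not list among the eligible specialties. Nor can one infer that blood loss, a redosing trigger, will go unrecorded. The checklist is a template, and the data lists in sections 3.1.1 and 4.1 are open-ended.

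**Conclusion.** The point holds for endpoint 4, on the condition that the adopted package keeps a redosing step. As worded, the endpoint drops patients redosed on a trigger and keeps those with a trigger who were not redosed, so it can move against the package's intent.

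The size is not derivable from the protocol. It is the product of three unknown shares. Under the assumed trigger share and redosing change, 6-15 points is an upper bound and about 1-3 points applies if only a fifth of triggered patients have no post-operative doses. The background reports that prophylaxis is often continued beyond a day, so the lower end is plausible at baseline. The distortion grows as continuation falls, which is what the study hopes to achieve.

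For endpoint 5 the only gap is the unstated start of the clock. This is a clarification of two secondary endpoints and does not affect the primary analysis.

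**What to change.** When the package is finalised, reconcile endpoint 4 with it, leaving every dosing rule as the stakeholders set it. Define the endpoint in both phases as the percentage of patients given prophylaxis who had no post-operative prophylactic doses. Report intra-operative redoses separately, next to the recorded need for redosing. For endpoint 5, add that the 24 hours run from the end of surgery to the last dose, as checklist item 4 records, and apply this identically in both phases.

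The cost is the wording of two endpoints. Redosing and post-operative antimicrobials are already separate items in section 4.1, and the end of surgery is recorded there too. The template checklist adds the time of the last dose, which should also be confirmed on the baseline form. The small downside is that endpoint 4 is no longer a raw dose count. The raw figure can still be shown descriptively.
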